**Fig. 1 Fig1:**
[figure not shown]
Flow of registration and evaluation for this study. Participants will be randomized 1:1 into the intervention group or the waiting group. Participants will have seven intervention sessions, delivered over 4 months. Outcome measures will be evaluated at three times (T1–T3) in the intervention group and four times (T1–T4) in the waiting group

**Fig. 2 Fig2:**
[figure not shown]
SPIRIT figure: Schedule of enrollment, interventions, and assessments. *BDI-II* Beck Depression Inventory-II, *GAD-7* Generalized Anxiety Disorder-7, *FACT-G* Functional Assessment of Cancer Therapy-General, *FACIT-Sp-12* Functional Assessment of Chronic Illness Therapy - Spiritual Well-Being 12 Item Scale, *BADS-SF* Behavioral Activation for Depression Scale-Short Form, *VQ* Valuing Questionnaire, *NRS* Numerical rating scale, *IPOS* Integrated Palliative care Outcome Scale

Participants in the intervention group will be asked to complete questionnaires at three times (T1–T3). Participants in the waiting group will be asked to complete questionnaires at four times (T1–T4). They will complete questionnaires in the waiting room, at the examination room after the BA session at the facility, or at home. Research assistants will check the responses and ask participants to supply any missing data. The research assistants will collect the completed questionnaires. They will transfer the data from the questionnaires to the data center.

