**Methods:**

A randomized controlled trial with a wait-list control group (waiting group) of 38 patients with advanced cancer and depression will be conducted at three sites in Japan. The BA program consists of seven sessions. Outcome measures will be evaluated at three times in the intervention group; at the entry, at the end of the intervention and 4 months after the end of the intervention and four times in the waiting group: at the entry, before the intervention, at the end of the intervention, and 4 months after the end of the intervention. Primary outcome is Beck Depression Inventory-II (BDI-II) score. To examine the main effect of the intervention, two-way repeated measures analysis of variance (ANOVA) will be conducted, with timing and intervention status as the independent variables and BDI-II score as the dependent variable. One-way repeated measures ANOVA will be conducted to combine data from the intervention and control groups and examine changes in BDI-II scores by timing in both groups. Secondary endpoints (anxiety, quality of life, spirituality, degree of behavioral activation, value, and pain) will be evaluated with rating scales. Two-way repeated measures ANOVA will be conducted to examine whether there are differences between the groups before and after the intervention, with timing and intervention status as the independent variables and scores on each rating scale as the dependent variables.

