All therapists will be clinical psychologists or psychiatrists with clinical experience that includes working with patients with cancer and have sufficient experience conducting BA either during the pre-post study [26] or through BA training. A therapist is certified in BA training upon completion of the following three steps: (1) learning about the aims of BA, session structure, and how to proceed by attending an in-person or video training; (2) conducting BA with supervision at least once; and (3) being approved by a supervisor to perform BA.

The individuals responsible for measuring outcomes and assessing patients will differ from those who are responsible for conducting the program. While this program will not impact the patients’ regular treatment in any way, special psychotherapies such as BA (conducted elsewhere) and CBT are prohibited.

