The intervention and each assessment scale will be evaluated using the following process (Figs. 1 and 2). The University Hospital Medical Information Internet Data and Information System for Clinical and Epidemiological Research (UMIN INDICE) allocation software program will be used for case enrollment and randomization of intervention groups in this study. Randomization was stratified by study site with the minimization method to balance the gender (male, female) and the age of the participants at study entry (age 20 ≦ to < 40, age < 65, age 65 to < 100). For allocation concealment to research assistants who administer questionnaires, the allocation will be communicated to the person in charge at each site based on the allocation list prepared by the data center. In addition, the interval between T1 and T2, T2 and T3, T3 and T4 will be 4 months respectively, which is the same length of time it would take if the intervention group had implemented the program, so that research assistants will not be able to identify the allocation group based on the timing of evaluations. The allocation schedule will be kept at the data center until the end of the study. A psychiatrist or psychologist from each institution will be in charge of a total of seven intervention sessions. Outcome measures will be evaluated at three times (T1–T3) in the intervention group and four times (T1–T4) in the waiting group by research assistants who are not involved in the intervention program. Outcome measures will include the BDI-II score as the primary outcome measure and Generalized Anxiety Disorder-7 (GAD-7), Functional Assessment of Cancer Therapy-General (FACT-G), Functional Assessment of Chronic Illness Therapy - Spiritual Well-Being 12 Item Scale (FACIT-Sp-12), Behavioral Activation for Depression Scale-Short Form (BADS-SF), the Valuing Questionnaire (VQ), Numerical rating scale (NRS), and the Integrated Palliative care Outcome Scale (IPOS) scores as secondary outcome measures.

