### Outcomes

#### Primary outcomes

The primary outcome is the BDI-II score. The BDI-II is used to measure depressive symptoms. It consists of 21 self-reported items scored on a 4-point scale [27]. The psychometric criteria for the BDI-II are generally considered to be excellent when the instrument is administered to outpatients [27, 28]. Good reliability and validity have been reported for the Japanese version [29]. In order to ensure comparability with previous studies [24, 30, 31], we will use the BDI-II, which is similar to the scales used in previous studies. The BDI-II is widely used worldwide to assess subjective depression. We will compare whether there is a difference in BDI-II scores between the intervention group and the waiting group before and after the intervention.

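### Questionnaires may be completed right after a BA session, which at T2 only the intervention arm can do, so the setting of the self-reported BDI-II can differ by arm

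*Protocol article*

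**What the plan says.** The protocol article, Study procedure (text following the Fig. 2 legend), lists three places of completion: "They will complete questionnaires in the waiting room, at the examination room after the BA session at the facility, or at home". It ties none of them to an arm or a time point. The same paragraph gives the assistants a role in the content of the forms: "Research assistants will check the responses and ask participants to supply any missing data".

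The Abstract (Methods) sets the assessment times. For the intervention group they are "at the entry, at the end of the intervention and 4 months after the end of the intervention"; for the waiting group they are "at the entry, before the intervention, at the end of the intervention, and 4 months after the end of the intervention". The Fig. 1 legend adds: "Participants will have seven intervention sessions, delivered over 4 months".

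On masking, Study procedure makes the assessment intervals equal at four months, "so that research assistants will not be able to identify the allocation group based on the timing of evaluations". The Interventions section states: "The individuals responsible for measuring outcomes and assessing patients will differ from those who are responsible for conducting the program". Under Primary outcomes, BDI-II is described thus: "It consists of 21 self-reported items scored on a 4-point scale".

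**The concern.** A randomised comparison needs the outcome measured in the same way in both arms. Here one permitted setting is available to one arm only at the time point that matters most. A patient who rates mood in the therapy room minutes after a session, knowing that treatment has been received, may answer differently from a patient who fills in the form at home. A brief lift in mood, or a wish to give the therapist a good result, would be credited to BA as a treatment effect.

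There is a second, weaker strand. The plan tries to keep research assistants unaware of allocation, but its stated device removes only the cue from timing. At T2, a form handed over after a BA session identifies an intervention patient.

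**Working it through.** The plan gives no figure on this point, so there is none to reproduce. The check sets the schedule against the permitted settings, then illustrates the possible scale.

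**Step 1. When can a form follow a BA session?**

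| Time point | Intervention group | Waiting group |
|---|---|---|
| T1 | Before randomisation: no | Before randomisation: no |
| T2 | End of own programme: possible | Before own programme: not possible |
| T3 | Four months after programme: no | End of own programme: possible |
| T4 | Not assessed | Four months after programme: no |

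The post-session option can apply in only two cells: T2 in the intervention group and T3 in the waiting group. Both are end-of-treatment scores.

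**Step 2. Which analyses are touched?** Under Major statistical analysis, the two-way repeated measures ANOVA compares the arms. At T2, where only one arm has been treated, setting can differ by arm. At T3 the pattern reverses. The one-way ANOVA pools both groups over pre-intervention, post-intervention and four-month scores. There, only the post-intervention score can be taken just after therapy, so setting can be confounded with time.

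**Step 3. Does the last session fall at T2?** The Abstract and the Fig. 1 legend imply that it can. The Interventions section, however, has the seven sessions conducted over 1–2 weeks. If that means one session every 1–2 weeks, six gaps put session 7 at 6 × 1 = 6 to 6 × 2 = 12 weeks after session 1. Four months is about 17 weeks, so if session 1 comes soon after T1, session 7 would precede T2 by about 17 − 12 = 5 to 17 − 6 = 11 weeks. These statements must be reconciled. The post-session clause itself presumes that some assessment coincides with a session, and Step 1 leaves only the two end-of-treatment cells for that.

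**Step 4. Scale, by assumption.** The documents give no size for a setting effect. Let *d* be the shift in BDI-II in a patient who completes the form post-session and *p* the share of intervention patients who do so. The shift in the arm mean is *p × d*, to be set against the 3.5-point target (Power and sample calculation).

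- *p* = 1: *d* = 1 gives 1/3.5 = 29%; *d* = 2 gives 2/3.5 = 57%.
- *p* = 1/3: *d* = 1 gives 0.33/3.5 = 10%; *d* = 2 gives 0.67/3.5 = 19%.

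**Step 5. Effect on the one-sided 5% test, if the shift favours BA.** Inputs: 38 patients less 10% dropout is 38 × 0.9 = 34.2, about 17 per arm; SD 7.84. As a simplification, compare T2 scores by a two-sample test with normal approximation. The standard error is 7.84 × √(2/17) = 2.69. With no true effect and mean shift *b*, the false-positive rate is Φ(*b*/2.69 − 1.645).

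| Mean shift *b* (points) | False-positive rate |
|---|---|
| 0 | 5.0% |
| 0.5 | 7.2% |
| 1 | 10.2% |
| 2 | 18.4% |

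Here *b* is the arm-average shift *p × d*. A value of 0.5, for instance, arises if half the patients shift by 1 point.

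**The case against.** The strongest reply is that a permission is not a practice. Post-session completion is one of three options; the other two are open to both arms, and the waiting room is also at the facility. Session 7 may not coincide with T2 at all. This stands: how often the option would be used at T2 is unknown.

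A reader might infer that the masking of assistants is defeated. The documents do not support that. They do not say that the assistant is present in the examination room or is told where a form was completed, and assistants are kept apart from the programme. Because BDI-II is self-reported, an assistant who learned the arm could act mainly through checking answers and prompting for missing items. Unmasking is possible, with little route to the score.

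A reader might also infer a demonstrated bias in favour of BA. That is not shown either. No post-session mood effect is documented, and the section on patient disadvantages grants that the programme and questionnaires may cause stress, which could point the other way.

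It can be added that unmasked self-report against a wait-list is open to bias wherever forms are completed. True, but this increment is avoidable. Finally, a condensed article may omit operational detail that the full protocol holds. That would answer a complaint about silence; here the article expressly permits a setting that one arm cannot have at T2.

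**Conclusion.** The point holds as an avoidable, arm-specific measurement option. As written, the plan allows the setting of the primary outcome to differ by arm in the only randomised treated-versus-untreated contrast, and it allows a form collected after a session to reveal the arm to an assistant who is meant to be unaware of it. A bias in favour of BA is plausible; its direction and size cannot be established from the documents. They depend on how many patients use the option and on whether the last session falls at T2. The percentages and error rates above rest on assumed shifts and show only that, with about 17 patients per arm and a one-sided test, even a modest average shift would matter.

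It would go too far to say that nothing can be done in analysis. If the setting is recorded, a sensitivity analysis is possible. Its value is limited, because at T2 post-session completion occurs in one arm only and by choice, so it cannot be cleanly separated from the treatment effect. Prevention is the better remedy, and a change of wording should be made.

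**What to change.** - Remove the post-session option for T2, and for the waiting group's T3, which enters the pooled analysis.
- Require the same setting and procedure in both arms at each time point, for example at home or in the waiting room, before or apart from any BA session.
- Have forms returned to the research assistant without session information.
- Record the place and date of completion of every form, and use them in a sensitivity analysis.
- Reconcile the statements on programme length, so that the relation of the last session to T2 is clear.

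The cost is a change in procedural wording and two extra recorded items. Sample size and assessment times are untouched. Sessions are placed on hospital visit days where possible, so patients lose some convenience, and forms taken home carry a small risk of more missing data in a trial of 38. The existing check by research assistants can limit that risk.

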### Outcomes

#### Primary outcomes

The primary outcome is the BDI-II score. The BDI-II is used to measure depressive symptoms. It consists of 21 self-reported items scored on a 4-point scale [27]. The psychometric criteria for the BDI-II are generally considered to be excellent when the instrument is administered to outpatients [27, 28]. Good reliability and validity have been reported for the Japanese version [29]. In order to ensure comparability with previous studies [24, 30, 31], we will use the BDI-II, which is similar to the scales used in previous studies. The BDI-II is widely used worldwide to assess subjective depression. We will compare whether there is a difference in BDI-II scores between the intervention group and the waiting group before and after the intervention.

#### Secondary outcomes

Secondary outcomes consist of the change from the pre-intervention scores to the post-intervention scores on the following psychosocial measures: (1) GAD-7, (2) FACT-G, (3) FACIT-Sp-12, (4) BADS-SF, (5) VQ, (6) NRS, and (7) one item on pain in IPOS.

GAD-7 is a measure used to assess subjective anxiety. GAD-7 is a seven-item questionnaire developed to identify probable cases of GAD and to measure the severity of GAD symptoms [32]. A Japanese version has been validated [33]. The total score for GAD-7 ranges from 0 to 21.

FACT-G is a measure used to assess quality of life [34]. This widely used questionnaire consists of 27 items, with higher scores indicating higher QOL. The questionnaire comprises four domains: physical, social, emotional, and functional well-being.

FACIT-Sp-12 is a measure used to assess QOL that includes spirituality, which is important for patients with advanced cancer in clinical practice. It is a QOL assessment scale consisting of 12 items related to spirituality developed by Cella et al. [35, 36]. The rating scale is on a five-point scale from 0 (not at all applicable) to 4 (very applicable) with higher scores indicating higher QOL. The reliability and validity of the Japanese version have been confirmed [37].

BADS-SF is a measure used to assess the degree of BA and avoidance. BADS-SF was developed to assess changes in behavior resulting from BA [38]. BADS-SF comprises subscales about two traits, activation and avoidance. The Japanese version of this scale consists of eight items, which is one fewer than in the original version. The validity and reliability of the Japanese version have been confirmed [39].

VQ is a measure used to assess whether patients are engaging in value placing behaviors. VQ is a 10-item self-reported questionnaire that measures the degree to which one’s behaviors are consistent with their values [40]. A score of each item in VQ is calculated for each of the two factors, VQ Progress (VQ-P) and VQ Obstruction (VQ-O). VQ-P measures the extent to which individuals are aware of what is personally important to them and their perseverance in achieving whatever that is. VQ-O measures the extent to which living in line with one’s values is disrupted by avoiding experiences that distract from this goal, either due to neglect or a focus on other psychological experiences. The validity and reliability of the Japanese version have been confirmed [41].

NRS is a measure used to assess the degree of pain associated with physical symptoms. NRS asks for a pain score on a scale of 0 to 10, with 0 being no pain at all and 10 being the worst possible pain. It has been used in actual clinical practice and has been validated for both reliability and validity [42, 43].

One item on pain in IPOS assesses the extent to which pain interferes with life. IPOS is a holistic assessment instrument for palliative care that was validated in 2016 by Schildmann et al. The Palliative Care Outcome Scale (POS) [44] was developed in 1999 and its derivatives have been integrated as IPOS. A patient version and a staff version have been developed [45]. The validity and reliability of the Japanese patient version have also been verified [46]. The questionnaire uses a five-point scale from 0 (it did not disturb me at all) to 4 (it was unbearable) for the pain item in the Physical Symptoms section.

### Power and sample calculation

Based on the results of a previous study [47], the minimal clinically important difference of the primary endpoint, BDI-II, is 3.5 points. In our pre-post study of patients with cancer and depression [26], the standard deviation was 7.84 points. Many studies have demonstrated the effectiveness of BA in depression with a high level of evidence [23–25]. We hypothesized an alternative hypothesis that intervention group would have lower mean post-intervention scores on the BDI-II than waiting group. The sample size was calculated using a one-tailed test with α = 0.05, power (1-β) = 0.80, and r = 0.50 for the mean value of the two groups. Since 3 (9.4%) out of 32 participants dropped out of the aforementioned pre-post study [26], we assumed that 10% would drop out in this study as well, defined as patients that did not meet the exclusion criteria and discontinued participation. Thus, the total planned enrollment was set to 38 patients.

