## Duscussion

An important challenge in clinical oncology is determining which interventions are most acceptable and feasible to treat depression in patients with advanced cancer [11]. Though many studies have demonstrated the effectiveness of BA in depression with a high level of evidence [23–25], no studies have explored the effectiveness of BA in patients with advanced cancer.

This multicenter randomized controlled trial is the first study to assess the effectiveness of BA on depression in patients with advanced cancer. If this study can clarify the effectiveness of BA for patients with advanced cancer, our findings will provide evidence about the effectiveness of BA on depression and provide an intervention option that is acceptable and feasible for the treatment of depression in this population. The results of this study will lead to improved mood and rebuilding to regain life purpose and value in this vulnerable population. However, if the effectiveness of BA is not verified in this study, we will need to consider other approaches acceptable and feasible to treat depression in patients with advanced cancer.

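### A total of 38 patients does not give 80% power for a 3.5-point between-group difference; on the stated inputs power is about 36–38%, or 43–47% if baseline-adjusted

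*Protocol article*

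**What the plan says.** All inputs are in the protocol article, section Power and sample calculation:

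- Target difference: "the minimal clinically important difference of the primary endpoint, BDI-II, is 3.5 points".
- Variability, from the group's own uncontrolled pre-post study: "the standard deviation was 7.84 points".
- Error rates and correlation (the sentence ends by referring to both arms): "The sample size was calculated using a one-tailed test with α = 0.05, power (1-β) = 0.80, and r = 0.50 for the mean value of the two".
- Hypothesis: "intervention group would have lower mean post-intervention scores on the BDI-II than waiting group".
- Dropout: "we assumed that 10% would drop out in this study as well".
- Result: "Thus, the total planned enrollment was set to 38 patients".

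The caption of Fig. 1 gives the allocation: "Participants will be randomized 1:1 into the intervention group or the waiting group". The sections Primary outcomes and Major statistical analysis also put the primary question as a comparison of the two groups, by intention to treat, one-sided at 5%, with multiple imputation for missing data. No test or formula is named for the sample size calculation.

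**The concern.** The standardised difference is 3.5/7.84 = 0.446, a little under half a standard deviation. Comparing two independent groups on an effect of that size normally takes about 60 patients per arm at these error rates. The article plans 19 per arm, so the stated power and the stated hypothesis cannot both hold.

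What is at stake is how the result is read. A reader who trusts the 80% will take a non-significant result as fairly strong evidence against a 3.5-point benefit. At the power the trial really has, a true benefit of that size would be missed more often than found.

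**Working it through.** **Inputs.** Difference 3.5, SD 7.84, one-sided 5%, power 80%, r = 0.50, dropout 10%, total 38, allocation 1:1. Hence 19 per arm randomised; 38 × 0.9 = 34.2, so about 34 evaluable, 17 per arm. Power is from the noncentral t distribution. Reading r as the pre-post correlation is an assumption; the article's phrase is ambiguous.

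**1. Can 38 be reproduced?** Yes, but by more than one route, and none of them is a two-group test of 3.5 points.

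- *Paired, one-sided.* SD of a within-patient difference = 7.84 × √(2(1 − 0.5)) = 7.84, so the effect is 0.446. Power is 79.5% with 32 patients and 80.6% with 33. Made even for two arms this is 34, and 34/0.9 = 37.8, so 38. (Without that rounding, 33/0.9 = 36.7, so 37.)
- *Group-by-time interaction F-test*, 2 groups, 3 times, α = 0.05, f = 0.446/2 = 0.223, r = 0.5. Noncentrality = f² × N × 3/(1 − r). Power is 78.9% at N = 33 and 80.3% at N = 34; again 38 after dropout. With two time points this f means a between-group difference in change of 4 × 0.2232 × 7.84 = 7.0 points, twice the stated 3.5.
- *Taking 0.446 as Cohen's f in a two-group test.* This means d = 0.893, which is again 7 points. Power is 79.5% at 16 per arm and 81.7% at 17, so 34, then 38.

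**2. What the stated hypothesis needs.**

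- *Post-intervention scores.* SE = 7.84 × √(2/n). Power is 79.6% at 62 per arm and 80.2% at 63. Total 126 evaluable; 126/0.9 = 140 enrolled. A change-score analysis gives the same, because at r = 0.5 the change has the same SD.
- *Baseline-adjusted.* Residual SD = 7.84 × √(1 − 0.25) = 6.79. Power is 79.8% at 47 per arm and 80.6% at 48. Total 96 evaluable; 96/0.9 = 106.7, so 107 enrolled.

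**3. What 38 patients give for a true 3.5 points.**

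| | 17 per arm | 19 per arm |
|---|---|---|
| SE, unadjusted | 2.69 | 2.54 |
| Power, unadjusted | 35.5% | 38.4% |
| Power, baseline-adjusted | 43.1% | 46.6% |
| Detectable at 80%, unadjusted | 6.8 points | 6.4 points |
| Detectable at 80%, adjusted | 5.9 points | 5.6 points |
| 90% CI half-width, unadjusted | 4.6 points | 4.3 points |
| 90% CI half-width, adjusted | 3.9 points | 3.7 points |

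Every half-width exceeds 3.5. The interval can therefore exclude a 3.5-point benefit only when the estimate itself favours the waiting group.

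**The case against.** **The analysis is a repeated measures ANOVA, and two groups by three times is the layout that returns 34, then 38.** That layout does match the planned analysis. But an omnibus F-test is not the one-tailed test named in the calculation, and the effect behind it is about 7 points, so it does not support 80% power for 3.5. Nor do the later assessments rescue the power. Suppose a full 3.5-point difference held at both post-intervention times, all correlations were 0.5, and the mean of the two were adjusted for baseline. The residual SD would be 7.84 × √(0.75 − 0.25) = 5.54 and the power 56% to 60%. Even that comparison is not available: the waiting group is treated before its later assessments, so it has no untreated assessment matching the intervention group's 4-month follow-up.

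**Intention to treat with multiple imputation may analyse all 38.** This stands, and it is why the range runs to 19 per arm. That end assumes that imputation loses no information.

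**The baseline-adjusted figures belong to an analysis that the article does not specify.** This also stands. They show what adjustment could give, and they depend on the assumed meaning of r. The 36–38% does not.

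**Two stronger readings are tempting.** One is that 38 is certainly a paired, within-patient calculation wrongly attached to a randomised comparison. A reader might infer this from the fit and from the pre-post source of the SD. But other routes reach 38 as well and no test is named, so the documents do not establish it. The other is that the authors intend to treat a non-significant result as proof that the programme does not work. The Discussion says only: "if the effectiveness of BA is not verified in this study, we will need to consider other approaches". That is conditional and makes no claim of ineffectiveness.

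**Conclusion.** Wrong as written. No two-group calculation found with a 3.5-point difference, SD 7.84, one-sided 5% and r = 0.50 gives 80% power from 38 patients. The unadjusted shortfall rests only on the stated difference, SD, error rate, allocation and dropout. The total needed is about 2.8 times (107/38) to 3.7 times (140/38) the planned one. To reach 80% with 17 per arm, the SD would have to be about 7.84 × 3.5/6.83 = 4.0, or the baseline correlation about √(1 − (4.02/7.84)²) = 0.86; the article states 7.84 and 0.50.

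The fault is a mismatch between the hypothesis and the basis of the sample size. Which calculation produced 38 remains open, and the conclusion does not depend on it.

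**What to change.** Keep 38 patients. In Power and sample calculation, name the test that was used and the effect entered into it, and reconcile both with the between-group hypothesis. State what r = 0.50 refers to. Replace the 80% power claim with:

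> With 34 to 38 analysed patients, one-sided 5% and SD 7.84, power for a 3.5-point between-group difference is about 36–38% unadjusted (43–47% baseline-adjusted if r = 0.5); the trial has 80% power for a difference of about 6.4–6.8 points unadjusted (5.6–5.9 adjusted).

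Add that the primary between-group difference will be reported with its confidence interval, so that a non-significant result is not read as ruling out a 3.5-point benefit. A matching sentence in the Discussion would help but is optional.

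The cost is wording only: no extra patients and no change to conduct. The downside is that the stated power becomes less favourable.
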